## 8. Ethical Considerations

Ethics approval for this research has been granted by the Southern Cross University Human Ethics Committee (2020/133). Protocol variations will be submitted to HREC and notification to appropriate parties conducted according to HREC recommendations. Participants in this study have a mental illness and as such are a considered a vulnerable group. All staff involved in participant contact are experienced in dealing with mental illness. Recruitment processes will ensure participants have the capacity to provide informed consent. Additionally, ongoing participant capacity to consent will be monitored by Link Workers and study staff; lack of ability to consent will result in withdrawal and referral to appropriate services. Withdrawn participants will be given the option to exclude their data from analysis.

Participants’ welfare will also be ensured throughout the study via as-usual monitoring, assessment, and service referral from PCCS Link Workers; these referrals will be participant-specific and could include referral to a range of biopsychosocial services, such as psychological and psychiatric services (including medication review) or welfare services. This frequent contact with Link Workers will also aid in retention as arising issues that limit ability to participate (for example lack of transport) fall within the purview of the Link Worker role and can be addressed. Finally, the study design has inherent ethical advantages over RCTs or crossover designs, as all participants will have access to the intervention, and the intervention will not be removed over the course of the study [49].

## 9. Compensation for Potential Bias

Potential sources of bias have been identified based on the protocol paper by Bonnici, Gerry [73] who used a stepped-wedge design.

### 9.1. Lack of Blinding and Randomisation

Given the nature of the stepped-wedge design, participants and assessment staff will not be blinded. This limitation is somewhat attenuated by the random commencement of clusters into the intervention, and the use of control data [49]. Additionally the pragmatic (controlled trial allowing for longitudinal recruitment in multiple health services) and ethical advantages of this design are sufficient to compensate for this limitation [49].

### 9.2. Heterogeneity of Participant Clusters

Participants are likely to share characteristics within study sites, and within clusters due to stepped (delayed) commencement of groups across time—particularly in the current social climate (COVID-19). This limitation is considered in the statistical approach we will use [72] which allows for non-independence in the data including clustering and repeated measures.

### 9.3. Concurrent Treatments

Over the course of the study, participants will receive ongoing assessment and referral from PCCS Link Workers which may include, for example, psychological services or medication review. This concurrent care has the potential to confound assessment of the impact of the Forest Therapy intervention. However, this regular assessment and referral will be ongoing over the course of the entire study, and thus the same for both control and intervention time periods, limiting the confounding of these treatments. Furthermore, the vulnerable nature of participants with mental illness, and the length of the study (at least 25 weeks for each participant), requires consideration of the ethics and risk of withholding other treatments. Similarly, the translational nature of this research and the study sample (vulnerable participants accessing care services in the community) limits the capacity to control a variety of variables, including access to concurrent treatments.

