However, Australia’s first holistic SP programs for individuals with mental illness and disabilities have only been active since 2016, primarily implemented by NGO Primary and Community Services (PCCS) [33,34]. These ongoing programs offer care-coordination and community referral to local public, private, and community-run health and welfare services, in addition to internal and external social activities (e.g., art classes, coffee groups). Participants in these programs have demonstrated improvements in QoL and self-assessed health status [34], biopsychosocial wellbeing, reduced health service use, and frequency and confidence in participating in social activities [33].

A social activity that may be appropriate in the context of SP due to its holistic approach to wellbeing is Forest Therapy (FT) [35]. FT is a type of Nature Therapy and is based on the Japanese practice of Shinrin-Yoku or ‘Forest Bathing’, the goal of which is a mindful submersion in nature [36]. FT involves gentle walks in nature with a prescribed series of activities such as breathing exercises, exploring textures by touching items (e.g., trees, grass), drawing a ‘sound map’, or collecting natural objects to make a group artwork [36]. Mindful exposure to nature is demonstrated to decrease physiological arousal and have a ‘calming’ effect [37]. This may be because, for example, overstimulation in urbanised cities leads to cognitive overload and attention fatigue [38], and that returning to the environment for which we are adapted is restorative [39].

Time spent in nature is demonstrated to improve psychological wellbeing [40,41], boost immune function, and promote healing [35]. For example, a 2017 review [41] assessed six international studies of healthy, unwell (alcohol dependence, hypertension, COPD), and elderly adults completing short (1 h) to long (9 day) FT sessions and concluded FT can improve hypertension, cardiac and pulmonary function, immune function, inflammation, oxidative stress, and stress hormones. The same review demonstrated psychological improvements including decreases in self-report stress, depression, and anxiety [41]. A recent (2020) review [42] of the impact of FT on mental illness assessed 20 international studies of healthy and unwell (depression, alcohol dependence, chronic pain, metabolic syndrome, stroke) adults completing short (15 min) to long (4 h) FT sessions and concluded FT improves symptoms of depression, anxiety, and anger [42]

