### 1.2. Hypotheses

It is hypothesised that, compared to control data (initial 10-week assessment period for all participants), over the course of the FT intervention participants will show improvements in QoL, and psychosocial, psychological, and physical wellbeing.

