## 2. Methods

### 2.1. Design

This study will be a multi-site longitudinal stepped-wedge cluster randomised trial [49]. Each participant will complete an initial 10-week control period (with pre and post assessments) followed by the intervention in a group (cluster), thereby ‘acting as their own control’ [49]. Participants will be allocated to clusters in the order they enrol in the study, and commencement of each cluster will occur in random order [49]; randomisation will be conducted by author [name] using an online random permutation generator suggested by Suresh [50]. Randomisation information will be provided in writing to Link Workers at each site who will then liaise with the intervention clinician (author [name]) to commence clusters in the assigned order. Sites will complete the intervention sequentially.

Assessment timepoints include pre- and post-control period (assessments 1 and 2), pre- and post-intervention (assessments 3 and 4), and 5-weeks post intervention (assessment 5). Additional timepoints include pre (assessments A1–A10) and post (assessments B1–B10) all FT sessions. A flow diagram of study phases and assessment timepoints can be seen in Figure 1, below.

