### 2.2. Participants

The study aims to recruit 140 adults with ongoing mental illness (mood and psychotic disorders), living in the community at the Gold Coast (expected *n* = 45) and in Sydney (expected *n* = 95). Participants will be care-coordination clients of PCCS, an NGO that has previously developed and implemented SP programs in Australia [33,34]. PCCS has a steady flow of new care-coordination clients (who are referred by their GP) and these will form the recruitment pool. Eligibility criteria include:

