## 3. Recruitment and Informed Consent

Initial assessment and recruitment of participants will be conducted by PCCS ‘Link Workers’, who are experienced social workers or registered mental health nurses. Link Workers are responsible for the initial assessment, care-coordination and linkage, and ongoing management of PCCS client wellbeing. All new clients of PCCS will be assessed for eligibility during their initial intake assessment with their PCCS Link Worker. In addition to this eligibility assessment clients will receive their usual care from PCCS involving care-coordination and community referral to local public, private, and community-run biopsychosocial health and welfare services. Informed consent will be obtained by the Link Worker; they will provide clients a FT information brochure, the Participant Information Statement (PIS), and Participant Consent Form (PCF), allow sufficient time to read both, and answer all client questions. Link Workers will emphasise that clients are not required to participate in the research project to participate in the FT program, and they may withdraw their consent at any time. Clients will indicate consent by returning a signed PCF. All clients will also receive standard care from PCCS throughout the study.

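### Section 9.3 treats concurrent care as equal in both periods, but Forest Therapy always comes later after intake, so its effect is confounded with time in the care programme

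*Protocol article*

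**What the plan says.** - **Concurrent care (9.3).** Assessment and referral by Link Workers may confound the FT effect, but they run throughout the study "and thus the same for both control and intervention time periods, limiting the confounding of these treatments".
- **Who is recruited (2.2 and 3).** "PCCS has a steady flow of new care-coordination clients (who are referred by their GP) and these will form the recruitment pool". "All new clients of PCCS will be assessed for eligibility during their initial intake assessment with their PCCS Link Worker". Usual care begins alongside this: "In addition to this eligibility assessment clients will receive their usual care from PCCS involving care-coordination and community referral".
- **Order of conditions (2.1).** "Each participant will complete an initial 10-week control period (with pre and post assessments) followed by the intervention in a group (cluster").
- **What is randomised (2.1).** "Participants will be allocated to clusters in the order they enrol in the study, and commencement of each cluster will occur in random order".
- **The comparison (1.2).** FT is judged "compared to control data (initial 10-week assessment period for all participants").
- **What usual care does (1).** Of the provider's existing programmes, which are described as care coordination, referral and social activities with no mention of FT: "Participants in these programs have demonstrated improvements in QoL and self-assessed health status".
- **The model (7, Analysis, and 9.2).** A linear mixed model following a cited stepped-wedge method, relied on for clustering and repeated measures. Time since intake is not mentioned.

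**The concern.** Section 9.3 moves from care being offered throughout to care having the same influence in both periods. The second does not follow from the first. For a new client the control period falls near the start of a care programme. The FT period falls at least 10 weeks further in, when referrals have had time to take effect. If clients change after intake for any reason, whether benefit from the programme or natural recovery, that change lies between the two conditions.

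Randomising the order in which clusters commence does not solve this, because every participant still has control before FT. At stake is the central contrast: a programme with no FT effect could look effective, or a real effect could be hidden, while Section 9.3 tells the reader that this confounding is limited.

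**Working it through.** The plan gives no figure on this point to reproduce. The check sets the sections on a common clock and then asks what the comparison returns when FT does nothing.

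**1. Clock.** With no wait between periods, assessments 1 to 4 fall at weeks 0, 10, 10 and 20 of the trial schedule. The first three are before FT and the fourth is after it. Any wait before FT moves assessments 3 and 4 later still.

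**2. Inputs.** From the article: n = 126 (7.1), groups of 6 to 10 (4), and 10-week periods (2.1). Assumed:
- 14 clusters of 9 (14 × 9 = 126), with no wait.
- Week 0 is taken as intake; assessments 1 to 3 count as control and assessment 4 as FT.
- Variances are 0.05 (cluster), 0.55 (person) and 0.40 (residual), so the correlation within a person is 0.60.
- Calendar time enters as 5-week blocks.
- Usual-care curves g(t), in SD: (a) +0.3, all gained in weeks 0 to 10; (b) +0.1 per 10 weeks; (c) 0.4(1 − exp(−t/10)).

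**3. Formula.** The expected FT coefficient b is the FT element of (X′V⁻¹X)⁻¹X′V⁻¹g, and its SE is the square root of the matching diagonal element of (X′V⁻¹X)⁻¹. The two-sided 5% rejection rate is Φ(−1.96 − b/SE) + Φ(−1.96 + b/SE). The true FT effect is 0.

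| Cluster starts apart | SE | Bias (a), (b), (c), SD | Rejection rate |
|---|---|---|---|
| 2 weeks | 0.114 | −0.17, +0.04, −0.05 | 33%, 7%, 8% |
| 5 weeks | 0.087 | −0.02, +0.09, +0.08 | 6%, 19%, 14% |
| 10 weeks | 0.074 | +0.05, +0.12, +0.14 | 11%, 35%, 45% |

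Example, 10 weeks and curve (c): 0.136/0.0745 = 1.83, and Φ(1.83 − 1.96) = Φ(−0.13) = 0.45. The 33% at 2 weeks is almost all in the direction against FT.

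**4. The contrast matters too.** Take an assumed recovery of 9.7 points (0.5 × the stated SD of 19.4), again with no FT effect.
- Linear to week 20: values at weeks 0, 10 and 20 are 0, 4.85 and 9.70. The level difference, assessment 4 minus 2, is +4.85. The difference in changes is (9.70 − 4.85) − (4.85 − 0) = 0.
- Front-loaded, 9.7(1 − exp(−t/10)): values are 0, 6.13 and 8.39. The level difference is +2.26. The difference in changes is 2.26 − 6.13, about −3.9.
- Delayed (logistic, midpoint week 15): values are 0, 0.73 and 8.96. The level difference is +8.23. The difference in changes is 8.23 − 0.73 = +7.50.

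**5. When a calendar term would be enough.** If all clusters entered control together and crossed over at randomised steps, calendar time would equal time since intake, and the bias is 0 for every curve tried. Sections 2.1 and 2.2 describe something else: a steady inflow of clients, clusters filled in enrolment order and sites run in sequence.

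**6. Can time since intake be modelled?** With equal waits, a piecewise-linear term with a knot at week 10 gives (t − 10)₊ = 0, 0, 0, 10 at the four assessments. That is exactly 10 times the FT indicator 0, 0, 0, 1, so the model has rank 3 for 4 columns. With waits varied over 0 to 20 extra weeks the model is estimable: residual bias is at most about 0.02 SD and the SE is about 0.11 to 0.18 SD. A straight line alone is not enough, because it leaves a negative bias under the front-loaded curves (a) and (c).

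**7. Does removing assessment 1 from the control values help?** The calendar-adjusted bias becomes 0.00, +0.10 and +0.09 SD at every spacing. At 10 weeks that improves all three curves. At 2 and 5 weeks it is worse for (b) and (c), for example +0.04 to +0.10. The SE rises from 0.114 to 0.140 (23%) at 2 weeks, 0.0867 to 0.0885 (2%) at 5 weeks, and 0.0745 to 0.077 (3%) at 10 weeks.

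**The case against.** Section 9.3 already says that concurrent care may confound, claims only that this is limited, and admits that such variables are hard to control. The article does not state the interval from intake to assessment 1, and the study-phase figure is not available here. Groups of 6 to 10 have to fill, so some lag is possible, and the initial 10 weeks may describe the trial period rather than the first weeks of care. The Introduction gives neither the timing nor the size of the usual-care improvement. All of this stands, and it makes the size uncertain. It does not rescue the inference: a lag would shrink the difference in time since intake without removing it, because FT is still always later.

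Three stronger readings are tempting and are not supported.
- **That the bias must favour FT, with error rates of 34% to 78%.** Those rates come from a model with no time term, whereas stepped-wedge analyses normally carry period effects. With calendar adjustment the bias can go either way.
- **That the plan wrongly pools assessment 1 as a control value.** The article does not say which assessments enter the model. The sample-size section can be read as a post-period level contrast and the hypothesis as a contrast of changes.
- **That assessment 1 is taken at a low point, or that its 4-week count of GP visits includes the referral visit.** Neither the course of wellbeing nor the referral-to-assessment interval is given.

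**Conclusion.** The concern holds as a fault in the reasoning of Section 9.3 and as a limit on what the trial can conclude. By the article's own account, FT is always observed later than control in a programme whose clients are reported to improve. Neither random cluster order nor a calendar-period term separates the two under rolling enrolment.

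The documents support the existence of this confounding, not a particular size or sign. Under the assumed curves, with assessments 1 to 3 as control, no wait and no FT effect, the calendar-adjusted bias lies between about −0.17 and +0.14 SD, and rejection rates reach about 45% at 10-week spacing. These figures illustrate what is possible; they do not predict this trial's result. A reader might infer that the trial is bound to overstate FT, or that dropping assessment 1 would cure the problem. The calculations support neither.

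**What to change.** 1. **Section 9.3.** Replace the claim of equality with a statement that care is available in both periods, that FT comes later in the same programme, and that its effect is therefore confounded with time since intake. State the usual gap between intake and assessment 1.
2. **Data and Section 7, Analysis.** Record weeks since intake at each assessment. Section 5.1 makes questionnaires non-identifiable, so this has to be written on the form at the time. Where the wait between control and FT differs across clusters, add weeks since intake to the mixed model as a sensitivity analysis, in a form that allows early gains to level off.
3. **Equal waits.** State that FT cannot be separated from further time in the programme, and limit the conclusion accordingly.
4. **Optional.** Use assessment 1 only as a baseline covariate in a further sensitivity analysis, not as the remedy. With calendar adjustment, taking it out of the control values can increase the bias when clusters start close together, and it raises the SE by about 2% to 23%.

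The cost is revised wording, one extra field per assessment and a less precise sensitivity estimate (SE about 0.11 to 0.18 SD, against 0.074 to 0.114 for the calendar-adjusted model with equal waits). No further participants or visits are needed.

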## 10. Discussion

This paper details the protocol for a multi-site trial of a novel intervention for Australian adults with mental illness living in the community, and under the care of a care-coordination and linkage (SP) provider. It aims to assess the impact of SP FT on QoL and biopsychosocial wellbeing. This study will capitalise on the demonstrated physical and psychological benefits of FT and implement it in the context of SP, which may also elucidate potential benefits on psychosocial outcomes. If successful, this study will provide evidence for a truly holistic biopsychosocial intervention for mental illness which has hereto not been investigated.

This study will contribute to research by addressing many of the limitations of SP studies outlined in the review by Bickerdike and colleagues [22], including using a comparatively large sample size, inclusion of follow-up assessments, a control group, and the use of validated tools. It will also use a stepped-wedge randomised trial design thereby addressing the inconstant methodological rigour of previous studies. This study will also address the limitations of previous FT interventions which have not been widely implemented in the context of mental illness, but rather general psychological distress in largely non-clinical populations—for example, healthy university students, office workers, or adults with medical conditions such hypertension [74].

This study will contribute to clinical practice as SP FT has capacity for scalability, and thus the potential to provide a, affordable, holistic intervention for mental illness in community settings on a national scale (or indeed an international scale). An important characteristic that allows scalability is that SP is not limited to care-coordination and linkage organisations; SP in general, and SP FT specifically, can be based on referred from any healthcare worker. Importantly, evidence indicates that simply ‘signposting’ community activities (such as a GP providing a flyer) is not generally effective [75], and that someone in the community that has a more involved, long-term, ‘hands on’ relationship with the participant, and facilitates access to services, is more likely be effective [46]. This may be particularly important in regional and remote areas where access to GPs is limited [76]. Additional contributors to the scalability and affordability of SP FT are the flexibility of implementation of FT which can be adapted to any biome, facilitated by non-medical-professionals, and does not require any specialised equipment [47]. This scalability is particularly important contribution to clinical practice as mental illness is ubiquitous and represents a large portion of national burden of disease and government spending, both in Australia and globally.

## 11. Conclusions

This study will implement a novel intervention for mental illness that may demonstrate improvements in QoL and across biopsychosocial domains. If successful, it will provide evidence for a novel, holistic, scalable intervention for mental illness with the potential to be delivered both nationally, and internationally.

## Figures and Tables

**Figure 1 ijerph-17-09076-f001:**
[figure not shown]
Study phases and assessment timepoints.
